**Figure 2 F2:**
[figure not shown]
**Participant flowchart.** The study will span three phases of rehabilitation and recovery post-stroke: in-patient rehabilitation, out-patient rehabilitation, and post-rehabilitation community re-integration. Patients will be assessed for eligibility upon admission to in-patient rehabilitation and throughout their stay. Upon providing consent, participants will be assigned to either the feedback or no feedback group. Participants who are discharged to out-patient rehabilitation at one of Toronto Rehab sites will continue to complete the schedule of goal-planning for walking activity either with or without feedback (depending upon group allocation).

### Participants

Individuals with sub-acute stroke who are attending in-patient rehabilitation at Toronto Rehab will be recruited to this study and will provide written informed consent prior to participating. All participants will have identified improving walking function as a rehabilitation goal upon admission and will be able to walk without supervision at the time of recruitment into the study. Individuals unable to provide consent to participate in the study due to foreign language or cognitive impairment will be excluded. In order to ensure generalizability to the wider stroke population, no further exclusion criteria will be applied.

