### Current practice for goal setting and goal planning at Toronto Rehab

Goal setting and planning form an important part of care at Toronto Rehab. Goal setting is a patient-centred and collaborative process [27,28,35,36] wherein, upon admission to rehabilitation, the patient discusses goals with the interprofessional care team. Goals identified at this stage of care might be broad; e.g. “I want to be able to walk better”. Through discussion, the team explores the relationship of the individual’s goal and the impact of their condition within the context of participation and important life roles; e.g. “I want to be able to continue to provide childcare to my grandson, including walking him to school.” This part of the goal-setting and planning process is often termed ‘goal negotiation’ [27]. The individual therapists then work with the patient to identify specific and challenging [24,28] sub-goals at the activity or impairment level that would lead to progressive achievement of the larger goal; e.g. “I want to be able to walk 100m without stopping”. Each individual therapist then bases their therapeutic intervention on the patient’s identified goals. The goal coordinator, who is a member of the interprofessional team, meets with the patient once every two weeks to discuss progress towards all of his/her goals. Each individual therapist also meets with the patient routinely during daily therapy sessions to discuss progress relevant to his/her practice; i.e. physiotherapists would discuss progress towards walking goals with patients on a regular basis. During either the fortnightly meetings with the goal coordinator, or discussions with the patient’s therapists, sub-goals may be re-evaluated depending upon how the patient is progressing towards his/her goals; e.g. a more challenging goal may be set if previous sub-goals have been achieved. Specific goals are documented for each patient in the clinical chart. Throughout rehabilitation and at the time of discharge, the individual therapist or goal coordinator determines if the patient’s goals were achieved (see Figure 1).

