### Intervention

Participants will be recruited into the study when they are deemed to be ambulatory without supervision. Patients with stroke tend to be discharged from in-patient rehabilitation 2–4 weeks after they reach this status. Therefore, the length of the in-patient intervention phase will vary between participants but will be approximately 2–4 weeks long. Out-patient rehabilitation services are offered in three blocks of 4–6 weeks duration; the first block is 6-weeks long to allow extra time for assessment prior to prescription of rehabilitation services. Participants in this study will be followed only for the first and second (if applicable) block of out-patient rehabilitation. The third block is often either not completed at all or not completed immediately subsequent to the second block (i.e. there may be a gap of a number of months between the second and third block). Therefore, the duration of the out-patient phase of the intervention is 6–10 weeks.

In order to ensure that all physiotherapists administer the intervention in a consistent manner, we will host a series of in-services concerning goal-planning of walking activity. These in-services will focus specifically on the output from the ABLE system, which is the new component of this study. Physiotherapists will learn how to interpret the output from the ABLE system and how to use this information to evaluate a patient’s progress towards their goals. Specific cases will be discussed based on pilot testing of ambulatory monitoring.

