#### Secondary outcomes – self- efficacy, community integration, goal attainment, satisfaction & barriers

The Stroke Self-Efficacy Questionnaire (SEQ) [49] will be used to measure stroke-specific self-efficacy. This 13-item questionnaire asks participants to rate confidence in completing various tasks, including walking indoors and outdoors and exercising, on a scale from 0–10. This questionnaire shows good test-retest reliability (ICCs > 0.87) [50], internal consistency, and criterion validity and can discriminate between patients who are independently ambulating and those who are not [49].

The Community Integration Questionnaire (CIQ) will be used as a measure of integration and participation post-discharge from in- and out-patient rehabilitation [51,52] and has been used often in stroke research [53-56]. This is a 15-item questionnaire that evaluates integration into the community in three domains: home, social, and productive activities (e.g. employment or volunteer activities). Researchers have developed a version of the CIQ specifically for individuals with aphasia and this version of the questionnaire shows excellent test-retest reliability in the post-stroke population (ICC = 0.96) [55].

Goal attainment will be determined from patient charts at discharge from both in-patient and out-patient rehabilitation. Goals are classified ‘achieved’, ‘partially achieved’, ‘not completed’, or ‘discontinued’. Satisfaction with progress towards goals will also be extracted from patient charts (rated on a 10-point scale). We will interview patients in order to determine barriers to walking. A single open-ended question will be used: “what, if anything, do you think is preventing you from walking more than you are at the moment?”.

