### Statistical analyses and sample size

The following potentially confounding measures will be compared between the two intervention groups: CMSA, BBS, NIH-SS, ABC, and length of stay (in-patient rehabilitation). Measures that differ significantly between the two groups will be included as covariates in statistical models comparing interventions. Repeated-measures analysis of variance (ANOVA) or analysis of covariance (ANCOVA; as appropriate), with group-by-time interaction, will be used to evaluate the effect of the interventions on walking activity, spatio-temporal characteristics of walking, and SEQ. Separate ANOVAs will be used for each outcome measure. The ‘group’ term is the intervention group; the ‘time’ term is the assessment time point. The group-by-time interaction effect will reveal if there is a greater change over time in one group compared with the other. Separate analyses will be conducted to compare measures at the first three time points; i.e. discharge from in-patient will be compared to study enrolment, and discharge from out-patient will be compared to discharge from in-patient. One-way ANOVA or ANCOVA will be used to compare the CIQ and satisfaction between the two groups at discharge from rehabilitation and three months post-discharge from in-patient. The frequency of goal attainment between the two groups will be compared at discharge from both in-patient and out-patient rehabilitation; intent-to-treat analysis will be employed for this outcome for all participants initially randomized, including those who withdraw from the study [24,57]. Barriers to walking will be documented.

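### Goal attainment is read from the chart at discharge with no goal status recorded at entry, so goals achieved before randomisation are not excluded and would dilute this secondary comparison

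*Protocol article*

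**What the plan says.** All places are in the protocol article.

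- **Participants.** One sentence holds both eligibility conditions: "All participants will have identified improving walking function as a rehabilitation goal upon admission and will be able to walk without supervision". The walking goal is dated to admission. The functional condition is dated to entry: "will be able to walk without supervision at the time of recruitment into the study".
- **Intervention.** Entry follows functional status: "Participants will be recruited into the study when they are deemed to be ambulatory without supervision". Discharge from in-patient care tends to follow 2–4 weeks later. The Figure 2 legend has eligibility checked on admission and during the stay, with assignment after consent.
- **Current practice for goal setting and goal planning at Toronto Rehab.** Goals and sub-goals are set with the patient from admission and written in the chart. On when they are judged: "Throughout rehabilitation and at the time of discharge, the individual therapist or goal coordinator determines" whether they have been met. A harder sub-goal may follow one that is met.
- **Secondary outcomes.** "Goal attainment will be determined from patient charts at discharge from both in-patient and out-patient rehabilitation". There are four outcome categories, none of them dated relative to randomisation.
- **Measures, Table 1.** Goal attainment is marked at Times 2 and 3 and is blank at Time 1.
- **Statistical analyses and sample size.** "The frequency of goal attainment between the two groups will be compared at discharge from both in-patient and out-patient rehabilitation", by intent to treat.

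**The concern.** The record from which the outcome is read starts at admission. The intervention starts at randomisation, which can come later. A goal set in the first days of the stay and met before the patient could walk unsupervised is an achieved goal in the chart at discharge, in either arm, and feedback played no part in it.

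The secondary objective asks whether more walking during rehabilitation raises the rate of goal attainment. Goals settled before entry carry no information on that question. If they are counted, both arms' rates rise and the difference between them narrows. Because goal status is not recorded at entry, the analysts would later depend on whatever dates the charts happen to hold. Any sorting of goals into before and after would then be done once allocation is known to the treating therapists who keep those records.

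**Working it through.** **The plan's own figure.** The article gives no expected rate or power for goal attainment. Its only sample-size figure concerns change in walking duration: difference 20 min, SD 23 min, Type I error 0.05, Type II error 0.1.

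n per group = 2 × [23 × (1.960 + 1.282) / 20]² = 27.8, rounded up to 28.

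This reproduces the stated 28 per group with a two-sided test. It rests on an outcome measured at enrolment and at discharge, so the present point does not touch it.

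**The order of events.**

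1. Admission: goals are set and charted.
2. Between admission and enrolment: goals may be marked achieved, and sub-goals may be replaced.
3. Enrolment and randomisation: the patient walks unsupervised. No goal status is scheduled in Table 1.
4. About 2–4 weeks later, in-patient discharge: attainment is read from the chart.

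Nothing in the article limits step 4 to goals still open at step 3. The article does not give the usual length of stay, so the length of step 2 is unknown.

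**The size of the dilution.** Let f be the share of counted units (goals or participants; the article does not say which) already achieved at randomisation, taken as equal in the two arms. Let p_C and p_F be the true attainment rates in the control and feedback groups among the rest.

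Observed rate in an arm = f + (1 − f) × p

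Observed difference = [f + (1 − f) p_F] − [f + (1 − f) p_C] = (1 − f)(p_F − p_C)

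Assume p_C = 50% and p_F = 70%. Neither rate comes from the documents. Power is the two-sided 0.05 comparison of two proportions with one yes/no result per participant and 28 per arm.

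| f | Control | Feedback | Difference | Power |
|---|---|---|---|---|
| 0 | 50% | 70% | 20 points | 0.33 |
| 0.1 | 55% | 73% | 18 points | 0.29 |
| 0.2 | 60% | 76% | 16 points | 0.25 |
| 0.3 | 65% | 79% | 14 points | 0.21 |
| 0.5 | 75% | 85% | 10 points | 0.15 |

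With an assumed 40% v 70%, power falls from 0.62 at f = 0 to 0.46 at f = 0.2 and 0.27 at f = 0.5.

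**The case against.** The strongest reply is that this is silence, not error. The article does not say that goals closed before randomisation will be counted. The unit and denominator of a secondary outcome are details that a condensed article may leave to the full protocol or analysis plan. A blank at Time 1 is also natural for an end-of-phase measure. This stands in part: a later document could define the window. What the article does fix is the source of the outcome, when it is read, its categories, the comparison and the assessment schedule, and that schedule does not provide for recording goal status before allocation.

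The second reply is that f may be small. Sub-goals are replaced by harder ones as they are met, and walking goals continue to be discussed after entry in both arms. That makes it likely that most participants have an open goal, and f near zero cannot be ruled out. It does not close the gap, because an early sub-goal that is met and replaced can still stand in the chart as achieved.

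A reader might go further and infer that the eligibility criterion is faulty: that it admits patients whose walking goal is already met, on whom feedback cannot work. The documents do not support this. The required goal is to improve walking function, and walking unsupervised does not by itself fulfil it. The example goals under goal setting and in Figure 1 (walking better, 100 m without a stop, taking a grandson to school) all go beyond walking alone. Goals can be renewed, and feedback is also used to check an assigned walking programme. The article keeps entry broad on purpose ("no further exclusion criteria will be applied"), and narrowing it would give up some of that generalisability.

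**Conclusion.** The point holds for the outcome and not for eligibility. As written, goals achieved before randomisation are not excluded from the attainment comparison, and counting them would multiply the expected difference by (1 − f). On the illustrative 50% v 70%, that means 20 points at f = 0 down to 10 points at f = 0.5. This assumes that f is the same in both arms and that such goals are in fact counted.

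The severity is minor, for these reasons:

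- Goal attainment is a secondary outcome.
- What happened before randomisation cannot depend on allocation, so the expected effect is dilution and neither arm is systematically favoured.
- The primary walking measures have an enrolment baseline, and the 28 per group rests on one of them.
- On the illustrative 50% v 70% the comparison has low power even without dilution (0.33), so the fix removes a distortion but does not make the comparison strong.

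**What to change.** Add a goal-status entry to Table 1 at Time 1: before allocation, extract from the chart which goals are open and which are already closed. In the statistical section, state that the attainment comparison counts only goals open at randomisation or set after it, at both discharge points. Leave the eligibility criterion as it is.

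The cost is one extra chart extraction per participant, from records already kept, for about 62 participants, and somewhat fewer goals in the comparison. The extraction should be prospective. A reconstruction after discharge would depend on chart dates and would no longer be made before allocation.

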### Group allocation and blinding

Participants will be assigned using a blocked stratified randomization approach to one of two groups: 1) feedback of walking activity; or 2) no feedback of walking activity (i.e. control group). There will be two strata based on the factor walking speed. Walking speed predicts the level of community ambulation achieved following discharge from rehabilitation [5]. A threshold walking speed of 0.42 m/s has been found to be predictive of community ambulation post-stroke [32]; therefore, participants will be stratified according to self-selected walking speed (slow walkers: <0.42 m/s; moderate-fast walkers: ≥0.42 m/s). Stratification will help to ensure that the two groups do not differ significantly on this factor [33,34] and that there will be approximately equal numbers of participants assigned to each group. The block size within strata will be four participants.

Group allocation will be performed by the principal investigator. A computer-generated random sequence will be used to assign participants. The treating physiotherapists will administer the goal-setting/planning (including feedback, if appropriate). A blinded research assistant will conduct the assessments and process data. Participants cannot be blinded to group allocation and will be informed of the chance of being allocated to one of two groups.

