## Methods

### Design overview

This is a single-blind randomized controlled trial with the assessor being blinded to the group allocation (participants cannot be blinded to group allocation). Participants will be randomly assigned, using allocation concealment, to one of two groups: feedback or no feedback. The study will span three phases of rehabilitation and recovery post-stroke: in-patient rehabilitation, out-patient rehabilitation, and post-rehabilitation community reintegration. Outcome measures will be obtained at up to four time points (Figure 2): 1) upon entry into the study; 2) immediately prior to discharge from in-patient rehabilitation; 3) immediately prior to discharge from out-patient rehabilitation (for those admitted to out-patient rehabilitation at the institution); and 4) three months following discharge from rehabilitation. This study was approved by the University Health Network research ethics board (protocol number 11-027-DE).

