#### In-patient rehabilitation phase

Participants in both intervention groups will meet with their primary treating physiotherapist once per week to discuss progress towards their goals for rehabilitation that are relevant to physiotherapy, including goals for walking. All participants will wear the accelerometers every weekday during in-patient rehabilitation to monitor daily walking activity. Research personnel will meet with the patients each morning to ensure that the accelerometers are worn correctly.

For those participants assigned to the feedback group, physiotherapists will receive a daily summary of patients’ walking activity as a tool to guide goal planning. Physiotherapists will use the information as a ‘homework checker’ to determine if patients are complying with an assigned walking program. In the case of non-compliance, the physiotherapist will discuss a coping strategy for better integrating walking activity into the patients’ day. In the event that the patient is meeting their specific sub-goals for walking activity, the physiotherapist will re-evaluate these sub-goals and suggest more challenging goals.

For participants assigned to the control group, physiotherapists will not receive accelerometer-based feedback of daily walking activity. However, physiotherapists will still discuss the achievement of walking goals with their patient. The same strategies implemented in the feedback group will be implemented in the control group (i.e. action plans, coping strategies, re-evaluation of goals). This process is no different to usual care around goal planning at Toronto Rehab.

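### With a fixed, published block of four, up to a third of assignments (about 20 of 62) can be deduced by anyone who knows every earlier allocation in the stratum

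*Protocol article*

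**What the plan says.** **Sequence.** Under Group allocation and blinding: "Participants will be assigned using a blocked stratified randomization approach to one of two groups". The same section adds "There will be two strata based on the factor walking speed", cut at 0.42 m/s, and "The block size within strata will be four participants". No variation in block size is mentioned. The 1:1 ratio is my inference from the aim that "there will be approximately equal numbers of participants assigned to each group".

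**Who allocates.** "Group allocation will be performed by the principal investigator", from a computer-generated sequence. The Design overview states concealment without describing its mechanism: "Participants will be randomly assigned, using allocation concealment, to one of two groups: feedback or no feedback".

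**Who knows the arm.** The Design overview describes a single-blind trial: the assessor is blinded and participants are not. Treating physiotherapists deliver the goal planning, and reports reach them for one arm only: "For those participants assigned to the feedback group, physiotherapists will receive a daily summary" (In-patient rehabilitation phase). Patients in both arms wear the accelerometers.

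**How patients enter.** "Participants will be recruited into the study when they are deemed to be ambulatory without supervision" (Intervention). The legend of Figure 2 says that eligibility is assessed at admission and through the stay, and that assignment follows consent.

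**The concern.** Concealing the list and making the next assignment unpredictable are two different protections. When the block size is constant and published, the second is lost towards the end of each block for anyone who has kept count. Assessor blinding protects measurement; it does nothing at the point of entry.

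Three features make this matter here. Some of the people close to recruitment know arms. Entry rests on a judgement that can be revisited during the stay. And the timing of entry bears on the outcome: the sample size is based on change in daily walking time from the initial assessment to in-patient discharge, and the Intervention section says discharge tends to follow unsupervised walking by 2–4 weeks. Someone who foresaw the next arm and could influence when a patient is enrolled would affect both the baseline value and the length of the period over which change is measured.

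**Working it through.** **Inputs.** Block size 4, two strata, about 62 recruited (protocol article). Equal allocation, so 2 + 2 in each block (inferred). An assignment counts as certain when one arm has already used both its places in the block.

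**The plan's own figure.** With a difference of 20 minutes, SD 23, two-sided alpha 0.05 (two-sidedness assumed) and power 0.90: n = 2 × (1.960 + 1.282)² × 23² / 20² = 27.8, so 28 per group, as stated. 56 × 1.10 = 61.6, which gives the stated figure of about 62. (56 / 0.90 = 62.2, or 63 rounded up, which is also within what the article calls approximate.)

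**Certain assignments in a full block.** The six possible orders are equally likely.
- First and second: never certain.
- Third: certain if the first two went to the same arm, probability 1/3.
- Fourth: always certain.
- Sum: 1/3 + 1 = 4/3 per block; (4/3) / 4 = 33.3%.

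**Best guess in a full block.** By position, the probability of guessing right is 1/2, 2/3, 2/3 and 1. Sum 2.833; 2.833 / 4 = 70.8%, against 50% with no information.

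**Applied to this trial.** With 31 per stratum there are seven full blocks and three places of an eighth: (7 × 4/3 + 1/3) / 31 = 9.67 / 31 = 31.2%, or 19.3 of 62 over both strata. Simulating 62 participants with a random split between strata gives 32.0%, or 19.8 of 62. Unequal strata (30:70 or 20:80) hardly change this.

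**Partial knowledge.** Suppose an observer knows the block boundaries but sees each earlier allocation only with probability v. Certainty at the third or fourth place requires having seen the two assignments that filled one arm, so the share in full blocks becomes v²/3:
- v = 0.75: 18.8% (simulated for 62 participants: 17.9%)
- v = 0.50: 8.3% (8.0%)
- v = 0.25: 2.1% (1.9%)

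The values of v are assumptions; the article gives none.

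**Varied block sizes.** Simulated with 31 per stratum and an observer who sees every earlier allocation and knows the possible sizes, but not the current one:

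| Block sizes | Certain | Best guess right | Largest within-stratum imbalance |
|---|---|---|---|
| 4 only | 31% | 70% | 2 |
| 4 and 6 | 5.7% | 68.6% | 3 |
| 4, 6 and 8 | 2.3% | 67.2% | 4 |

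The largest imbalance is half the largest block. In participants, the certain share falls from about 19 of 62 to 0.057 × 62 = 3.5 or 0.023 × 62 = 1.4. Correct best guesses fall from 0.698 × 62 = 43.3 to 42.5 or 41.7.

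**The case against.** The strongest reply is that one third is a ceiling which few people could reach. It needs the block size, the block boundaries, each patient's stratum and every earlier allocation in it. The article shows only that a physiotherapist knows the arm of his or her own patients. The device is worn in both arms, so it reveals nothing to others, and the stratum of a colleague's patient would have to be known or guessed. This stands. A reader might infer that treating staff can foresee a third of assignments; the article does not support that. The principal investigator, who performs the allocation, is the clearest candidate for full knowledge.

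Second, a reader might infer that entry has been or will be manipulated. The article does not say who judges readiness or who enrols, and it limits discretion by applying few exclusion criteria. No bias in minutes of walking can be derived from it. That also stands.

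Third, a reader might call the trial unblinded. It is single-blind with a blinded assessor, although this does not bear on selection at entry.

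Fourth, the plan has some protection: stratification by walking speed, a baseline measurement of walking activity, and a test of change through the group-by-time interaction. These limit the harm without removing it. Stratification balances only a two-level speed category, and covariates are added only if the groups differ significantly, a weak screen with about 28 per group.

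Last, varied blocks barely reduce guessing and do nothing against someone holding the list. Both are true. What they remove is certainty, the form of knowledge on which deliberate timing of entry could most safely rely. That a condensed article does not describe the concealment mechanism is no fault; the fixed block size, by contrast, is a choice it states.

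**Conclusion.** The point holds as a design weakness that is cheap to correct. It is neither an error nor a contradiction in the plan. With one fixed and published block size of four, at most 31–33% of assignments, about 20 of 62, can be deduced with certainty by someone with complete knowledge of the stratum. For a physiotherapist who knows only some of the earlier allocations the share is lower: about 18%, 8% or 2% at the assumed levels of visibility. The figures rest on 2 + 2 blocks, known block boundaries and, for the upper limit, every earlier allocation being known. Selective entry is a risk that stated concealment does not close. Whether it would occur, and how much bias it would cause, cannot be judged from the article.

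**What to change.** Generate the sequence with block sizes varied at random within each walking-speed stratum, for example 4 and 6, or 4, 6 and 8. Keep the sizes out of any material open to staff who recruit or treat.

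The work is a change to a computer-generated list. The price is a larger possible imbalance if recruitment stops inside a block: within a stratum, at most 3 (sizes 4 and 6) or 4 (sizes 4, 6 and 8) in place of 2; over both strata together, at most 6 or 8 in place of 4. Sizes 4 and 6 give most of the gain at the smaller price.

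This change does not cover a person who can see the list. Since the principal investigator allocates, the full protocol should make clear that whoever judges readiness or enrols has no access to it.
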